**Fig. 2 Fig2:**
[figure not shown]
Schedule of enrollment, interventions, and assessments

### Safety monitoring

Patients’ legal representatives will be informed of potential adverse events from acupuncture prior to signing the consent form. Any adverse events, including acupoint hematoma, infection, and apostasis, will be recorded by the researcher. In case of severe adverse events occurring, acupuncture intervention will be ceased immediately and proper treatment will be provided. All severe adverse events will be reported to the principle investigator and the ethics committee within 48 h. Patients will be followed up for 1 month after the trial.

### Sample size calculation

The purpose of this study is to clarify the role of acupuncture in the consciousness recovery of patients with TBI. Therefore, GCS change will be used as an evaluation index. Changes in GCS before and after treatment in our pilot study were shown to be 2.27 ± 3.52 (*n* = 11) in the control group and 3.70 ± 2.16 (*n* = 12) in the acupuncture group. Sample size was calculated using the following formula:$$ n={\left[\frac{\left({Z}_{\alpha /2}+{Z}_{\beta}\right)\sigma }{\delta}\right]}^2\left(\frac{1}{Q_1}+\frac{1}{Q_2}\right) $$where *n* represents the number of samples required, *n* = *n*_1_ + *n*_2_, Q_1_ = *n*_1_/*n*, Q_2=_
*n*_2_/*n* with 80% power and significance level at 5% for a two-sided test. Thus, allowing for 10% of attrition, we will recruit 150 participants, with 75 in each group.

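### The pilot acupuncture figures that size the trial (GCS change 3.70 ± 2.16, n = 12) do not fit together if GCS changes are whole numbers; they need checking before the stated power can be relied on

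*Protocol article*

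**What the plan says.** Under Sample size calculation, the protocol article picks the sizing variable ("GCS change will be used as an evaluation index") and takes its inputs from the authors' own pilot: "2.27 ± 3.52 (*n* = 11) in the control group and 3.70 ± 2.16 (*n* = 12) in the acupuncture group". It prints a normal-approximation formula for comparing two means, "with 80% power and significance level at 5% for a two-sided test", and concludes: "Thus, allowing for 10% of attrition, we will recruit 150 participants, with 75 in each group".

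The section does not print the difference δ or the common SD σ that went into the formula. It reports no missing pilot patients and no averaging of repeated GCS ratings.

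**The concern.** GCS is scored in whole points, so a patient's before-to-after change is a whole number. A mean of n such changes must be a multiple of 1/n, and with small n only a few two-decimal means are possible. The same holds for the SD. The printed acupuncture mean and SD both fail this test at n = 12.

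The pilot is the only basis the article gives for the assumed difference, its SD, the 80% power and the 150 patients. An error confined to the printed n would hardly matter. An error in the mean or SD, or patients missing from the summary, could change the effect that the trial claims to be powered for.

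**Working it through.** **Inputs** (all from Sample size calculation): control mean 2.27, SD 3.52, n = 11; acupuncture mean 3.70, SD 2.16, n = 12; two-sided 5%, 80% power, 10% attrition, 1:1 allocation, 150 recruited. δ = 3.70 − 2.27 = 1.43. σ is not stated; I assume the pooled pilot SD.

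**1. The plan's own figure.** With Q₁ = Q₂ = 0.5 the formula becomes N = 4 × [(1.960 + 0.842) σ/δ]².

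- n = 11 and 12 as printed: σ² = (10 × 3.52² + 11 × 2.16²)/21 = 8.344, so σ = 2.889. N = 128.1 evaluable, and 128.1/0.9 = 142.3 recruited. Rounding up within arms gives 65, then 73 per arm, or 146 in total.
- n = 11 and 10: σ² = (10 × 3.52² + 9 × 2.16²)/19 = 8.731, so σ = 2.955. N = 134.1 evaluable, 148.9 recruited.
- Unweighted SD: σ = √[(3.52² + 2.16²)/2] = 2.920. N = 130.9 evaluable, 145.5 recruited.

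The stated 150 is close to all three.

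**2. Whole-number check.** Let S be the sum of the changes and Q the sum of their squares. S/n must round to the printed mean, and √[(Q − S²/n)/(n − 1)] must round to the printed SD. Because a whole number and its square are both odd or both even, Q and S must be both odd or both even.

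- *Control, n = 11.* S = 25 gives 25/11 = 2.273. Q = 181 gives √[(181 − 56.82)/10] = 3.524. Both figures fit.
- *Acupuncture, n = 12, mean.* 44/12 = 3.667 and 45/12 = 3.750. No sum gives 3.70. Half-point scores do not help: 89/24 = 3.708 is the nearest.
- *Acupuncture, n = 12, SD.* This covers the chance that 3.70 is a coarsely rounded 3.7. For S = 44, Q = 212 gives 2.146 and Q = 214 gives 2.188. For S = 45, Q = 219 gives 2.137 and Q = 221 gives 2.179. None is 2.16. With divisor n the nearest values are 2.134 and 2.173 for S = 44, and 2.165 (which rounds to 2.17) for S = 45.
- *Acupuncture, n = 10.* S = 37 gives 3.70. Q = 179 gives √[(179 − 136.9)/9] = 2.163. Both fit, and real data can produce them (for example 0, 0, 2 and seven 5s). Of all sizes from 5 to 20, only n = 10 gives both printed figures.

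**3. What it does to power.** With 135 evaluable (150 × 0.9), power = Φ(δ/σ × √(135/4) − 1.96).

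- As printed (σ = 2.889): Φ(2.876 − 1.96) = 82.0%.
- If n was 10 (σ = 2.955): Φ(2.811 − 1.96) = 80.3%.

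Now suppose 12 were treated, the summary covers 10 of them, and the other two each changed by x. Then S = 37 + 2x and Q = 179 + 2x² over 12 patients. The values of x are assumptions; the article gives none.

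| x for each | Mean | SD | δ | Pooled σ | Power, 135 evaluable |
|---|---|---|---|---|---|
| 0 | 3.08 | 2.43 | 0.81 | 3.00 | 35% |
| +2 | 3.42 | 2.07 | 1.15 | 2.85 | 65% |
| +3 | 3.58 | 1.98 | 1.31 | 2.82 | 77% |
| +4 | 3.75 | 1.96 | 1.48 | 2.81 | 86% |
| +6 | 4.08 | 2.15 | 1.81 | 2.89 | 95% |

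**The case against.** The strongest reply is that the check rests on whole-number changes. If each patient's value were an average over several ratings, 3.70 with n = 12 might be possible. That limit is real, but the article mentions no averaging. The control arm also passes the check on both figures, although with n = 11 only 11 of the 100 possible two-decimal endings of a mean are attainable. That favours whole-number changes without proving them.

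The second reply is that the practical effect may be nil: if 12 is a misprint for 10, δ and both SDs are right and the correction is one number. That stands.

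A reader might go further in three ways that the article does not support.

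- *That the pilot arm had 10 patients.* The figures fit 10 and do not fit 12, but a mistyped mean or SD with a correct n of 12 is also possible. Nor does the total of 150 settle it. σ is unstated, and 142 to 149 recruited, depending on its choice, could each have been rounded up to 150.
- *That two patients were dropped and 1.43 is therefore too large.* The article reports no pilot losses. If there were any, the table shows that power could be lower or higher than stated.
- *That 150 is wrong, or lacks a margin.* A trial sized for 80% power after attrition has about 80% by construction. That is not a fault.

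**Conclusion.** The point holds as an inconsistency. If GCS changes are whole numbers, the printed mean and SD of the pilot acupuncture arm cannot come from 12 patients. At least one of mean, SD or n is misreported, or the summary leaves patients out. Only the pilot records can show which.

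The size of the consequence depends on the cause. A misprinted n moves power from 82.0% to 80.3% and leaves 150 standing. Two omitted patients would put it anywhere from about 35% to 95% over the assumed values shown. These power figures also assume a pooled SD, the protocol's normal formula and exactly 10% attrition. The finding does not show that the trial is underpowered. It shows that the sole stated basis for its power needs to be verified.

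**What to change.** Recheck the 23 pilot records and correct or explain the acupuncture n, mean and SD under Sample size calculation. State the δ and σ used in the formula. Then restate the power that 150 recruited (135 evaluable) gives for the corrected values, keeping the sample size at 150.

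- If 10 patients were analysed, print n = 10 with δ = 1.43 and σ = 2.95; power is about 80%.
- If 12 were treated and some are missing from the summary, recompute mean and SD on all 12 and report the resulting power, whichever way it moves.
- If the mean or SD was mistyped, print the right value and recompute.
- If the changes were averages over several ratings, say so.

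The cost is a short record check and a corrected paragraph. The stated power may become less favourable. No extra patients are needed, and no endpoint or analysis changes.

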### Statistical analysis

SPSS 17.0 (IBM SPSS, Chicago, IL, USA) will be used to analyze the data. Quantitative data will be presented as mean ± SD. Single factor variance analysis will be used to compare the difference in heart rate, blood pressure, mean arterial pressure, respiratory rate, and saturation of pulse oxygen between the two groups. The χ^2^ test will be used to compare the incidence of complications and adverse events between groups. Measurement of neural function recovery, including GCS, Glasgow Outcome Scale, and activities of daily living, will be analyzed using rank sum-test. Longitudinal changes in MMN amplitude will be analyzed using a mixed model procedure. *P* values of less than 0.05 will be considered statistically significant.

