### Participants

A total of 150 patients with TBI being treated at West-China Hospital of Sichuan University will be enrolled in this study after the legal representative signs the informed consent. The inclusion, exclusion, and withdrawal criteria are described in Table 1.

**Table 1 Tab1:** Inclusion and exclusion criteria for electro-acupuncture in severe traumatic brain injury trial

Inclusion	Patients with severe traumatic brain injury admitted to ICU: • Initial GCS score less than 8 points on admission • Estimated ICU stay longer than 2 weeks • Normal consciousness level before brain injury, no primary disorders in cognitive or motor function • Aged from 18 to 75 years • Agree to participate in the study and sign the informed consent
Exclusion	Patients are excluded from the study if any of the following criteria apply: • Vital signs are not stable on admission, die within 24 h • Women with pregnancy • Legal representative or immediate family has no strong treatment intent, can withdraw from treatment within 1 week • Patients with multiple trauma associated with limb fracture or skin defect
Withdrawal	Patients will be withdrawn from the study if any of the following criteria applies: • Life-threatening complications • Secondary hydrocephalus • Uncontrolled intracranial infection • Re-operate due to varieties of causes • Massive cerebral infarction • Unable to follow-up

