### Outcome measures

The primary measurements for efficacy assessment will be changes in Glasgow Coma Scale (GCS) and MMN. Additionally, Glasgow Outcome Scale and Barthel Index of Activities of Daily Living at 3 months after the trauma will be compared between the two groups. Secondary measurements will be the length of stay in ICU and hospital, expenses in ICU and hospital, and the incidence of coma-related complications. Safety will be assessed by monitoring adverse events as well as changes in vital signs during the study (see Fig. 2 and Additional file 1: Standard Protocol Items: Recommendations for Interventional Trials (SPIRIT) Checklist).

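### The main GCS comparison is an unadjusted rank-sum test that leaves open what is ranked, makes little or no use of the pre-treatment GCS, and gives no estimate of the 1.43-point difference used for sizing

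*Protocol article*

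**What the plan says.** Under Outcome measures the protocol article states: "The primary measurements for efficacy assessment will be changes in Glasgow Coma Scale (GCS) and MMN". Sample size calculation then singles out GCS: "Therefore, GCS change will be used as an evaluation index". That section uses a normal-theory formula for a difference in means, with pilot changes of 2.27 ± 3.52 (control, n = 11) and 3.70 ± 2.16 (acupuncture, n = 12).

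Statistical analysis fixes the test: "Measurement of neural function recovery, including GCS, Glasgow Outcome Scale, and activities of daily living, will be analyzed using rank sum-test". No covariate is attached to it, and the sentence does not say whether the ranked quantity is the change or the score after treatment. Quantitative data are to be summarised as mean ± SD. MMN, the other primary measure, is to be analysed with a mixed model.

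Two early GCS values are in play. Table 1 sets an entry limit: "Initial GCS score less than 8 points on admission". The pilot change, by contrast, is measured from before to after treatment, and Procedure starts acupuncture 3 days after trauma, or later if the patient is unstable.

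**The concern.** The trial is sized on a difference in mean change but tested with a procedure that does not estimate one. Three consequences follow.

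- **Ambiguity.** Ranking the change and ranking the final score are different analyses with different power. The article allows either.
- **Baseline use.** Ranking the final score ignores where the patient started. Ranking the change subtracts the starting value with a slope of exactly 1, which need not be the right slope on a bounded scale: a pre-treatment score of 3 leaves 12 points to gain, and a score of 7 leaves 8. The Glasgow Outcome Scale and the Barthel Index get the same unadjusted test, without even that subtraction.
- **Estimate.** A rank-sum P value does not tell a reader how many GCS points were gained or how precisely that is known.

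**Working it through.** **1. The plan's own sample size.** Inputs from Sample size calculation: δ = 3.70 − 2.27 = 1.43; 80% power; two-sided 5%; 10% attrition; 1:1 allocation. The common SD is not printed. I take the root mean square of the pilot SDs: σ = √[(3.52² + 2.16²)/2] = 2.92.

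- Per arm: 2 × [(1.960 + 0.842) × 2.92 / 1.43]² = 65.5, so 66; total 132; 132/0.9 = 147.
- With the exact t-test: 67 per arm; 134/0.9 = 149.

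Both agree with the planned 150.

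**2. Cost of ranks alone.** With 135 completers (67.5 per arm), power for a comparison of means is 0.81. At the rank-sum efficiency of 3/π under normality it is 0.79. That is small and not the issue.

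**3. What imbalance can do.** Let r be the size of the correlation between pre-treatment GCS and change (not given; assumed). On the mean scale, a chance imbalance of 1.96 standard errors moves the unadjusted difference in mean change by r × 1.96 × 2.92 × √(2/67.5) = r × 0.985.

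- r = 0.2: 0.20 points, about 14% of 1.43.
- r = 0.4: 0.39 points, about 28% of 1.43.

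For the final score the shift is (1 + slope of change on baseline) × imbalance. With a baseline SD of 1.41 the 1.96-SE imbalance is 0.48 points. The shift is then 0.48 points at slope 0 but only 0.2 × 0.48 = 0.10 at slope −0.8. Which reading is more exposed therefore depends on a slope that nobody has stated.

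**4. Power of the competing analyses.** Simulation assumptions: GCS bounded at 3 to 15; pre-treatment GCS uniform on 3 to 7 (SD √2 = 1.41); pilot SDs by arm; true difference 1.43; 67 per arm; 3,000 trials per setting (simulation error about √(0.77 × 0.23/3000) = 0.008). Slopes of −0.4 and −0.8 correspond to r = √(0.4² × 2 / 2.92²) = 0.19 and √(0.8² × 2 / 2.92²) = 0.39.

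| Slope of change on baseline | Rank-sum, change | Rank-sum, final | Linear ANCOVA |
|---|---|---|---|
| 0 | 0.78 | 0.69 | 0.75 |
| −0.4 | 0.77 | 0.75 | 0.77 |
| −0.8 | 0.77 | 0.83 | 0.82 |

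A second simulation added a rank-based baseline-adjusted analysis as a stand-in for the ordinal model. Against rank-sum on change it gave 0.77 versus 0.77 at slope 0, and 0.82 versus 0.76 at slope −0.8. It also beat rank-sum on the final score except at the steepest slope, where the two were equal. Linear ANCOVA in that run gave 0.74 against 0.77 at slope 0.

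**5. Precision of an estimate in points.** With 67.5 per arm and r = 0, the 95% CI half-width is 1.96 × 2.92 × √(2/67.5) = 0.99 points. It narrows as r rises.

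**The case against.** The rank-sum test is valid under randomisation and conventional for bounded ordinal scales. A journal article may leave covariates, effect measures and stratification factors to a fuller document. Planned arm means allow a crude difference to be worked out. All of this stands, so the point is an improvement to a stated analysis and not an error. It is still a fair point, because the article does name the test for its sizing endpoint.

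A reader might infer more than the documents support:

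- **That adjustment would cut variance by 25% and lift power to 0.91.** This needs equal baseline and final SDs with a correlation of 0.5, hence a baseline SD equal to the change SD, about 2.9. On a 3 to 7 range the SD cannot exceed about 2. No document gives the correlation or the baseline SD.
- **That adjustment can never lose.** Linear ANCOVA falls about 3 points below rank-sum on change at slope 0, where the unequal pilot SDs favour ranks.
- **That baseline imbalance is wholly uncorrected.** This is so only if final GCS is ranked. Change already removes baseline with slope 1, leaving a residual.
- **That the entry limit fixes the baseline range.** The limit applies at admission, while treatment starts at least 3 days after trauma. The pre-treatment value may differ, so the 3 to 7 range above is an assumption.

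**Conclusion.** The concern holds as a cheap improvement. The planned test is sound and the sample size is not in question. What is left open or unused is the quantity ranked, the pre-treatment GCS (beyond any subtraction), and an estimate with a confidence interval for the effect used in sizing.

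The size of the power gain is uncertain. For slopes from 0 to −0.8, a rank-based adjusted analysis moves power against rank-sum on change from about no gain to about +6 points, and linear ANCOVA from about −3 to +5 or +6. These figures rest on the assumed baseline distribution, the pilot SDs and the assumed slopes. The rank-based analysis is a proxy; the ordinal model itself was not simulated. The case for an estimate and for a clear definition of the analysed score does not depend on any of these assumptions.

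**What to change.** - State which GCS value is the baseline (the one taken before treatment, not necessarily the one at admission) and which post-treatment value is analysed.
- Main GCS analysis: an ordinal (proportional-odds) model of post-treatment GCS on arm and pre-treatment GCS, reporting the common odds ratio with 95% CI.
- Add an ANCOVA of post-treatment GCS on arm and pre-treatment GCS, with robust standard errors because the pilot SDs differ (3.52 against 2.16). It gives the mean difference in points, with 95% CI, to set beside 1.43.
- Adjust the Glasgow Outcome Scale and the Barthel Index for baseline GCS in the same way.
- Keep the rank-sum test as a sensitivity analysis, stating whether change or final score is ranked.

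If a fuller analysis plan already contains this, align the article's wording with it. The cost is analysis wording only, with no new data or patients, and it should be settled before allocation is revealed to the analysts. The downside is a proportional-odds assumption to check.

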### Quality control

In order to avoid possible heterogeneity in the measurement data and to ensure high-quality data results, the study data will be manually recorded on the case report form and uploaded to the database. The trial management team will control data quality through regular meetings and strict trainings to ensure that the acupuncturists, intensivists, neurosurgeons, and nurses are fully aware of the complete procedure. When the clinical trial begins, the principle investigator will supervise the trial to ensure that (1) the recruited patients are within the scope of the planned number; (2) all participants meet the inclusion criteria; and (3) all participants follow the clinical trial process. Auditing trial conduct will be performed every 3 months by investigators, intensivists, and surgeons.

Mechanism studies using animal models have shown that electro-acupuncture may alleviate cerebral injuries via upregulation of transforming growth factor beta 1 [21]. Activation of large-conductance Ca^+^-activated K^+^ channels is also likely involved in the protective effects of GV26 [22]. Herein, in order to avoid variations in the acupuncture procedure, electro-acupuncture will be used to achieve good control of the depth, frequency, and duration of treatment.

ERP can provide important information on human brain functions. Among all the auditory ERP components, MMN is an automatic event related to brain response. MMN can be recorded in comatose patient and is considered a reliable predictor of awakening from coma, with a specificity of 91% [23]. When patients start to regain consciousness, there might be an enhancement of MMN amplitude prior to communicating with the environment. Herein, longitudinal changes in MMN responses will be investigated to identify early signs of recovery.

In conclusion, this study will provide solid evidence of the role of electro-acupuncture in the recovery of consciousness of patients with TBI.

### Trial status

Patient recruitment is ongoing. This is protocol version 20160701, version date is 2016.7.23. Recruitment was started in June 2017 and will be completed in June 2018.

## Abbreviations

DOC: Disorder of consciousness
ERP: Event-related potentials
GCS: Glasgow Coma Scale
MMN: Mismatch negativity
TBI: Traumatic brain injury
